### Assessment of QoL

#### Qualidem

The Qualidem is a reliable and valid 40-item questionnaire designed to determine QoL in institutionalized residents with dementia [109-111]. The questionnaire includes indicative and contra-indicative items that can be divided into 9 homogeneous subscales: 1) care relationship, 2) positive affect, 3) negative affect, 4) restless tense behaviour, 5) positive self-image, 6) social relations, 7) social isolation, 8) feeling at home, 9) having something to do. The items are printed in random order, so that items of a subscale are spread within the questionnaire. Each item has 4 possible responses; 'never', 'rarely', 'sometimes' and 'often'. Each response is scored with 0 to 3 points, with higher scores indicating higher QoL. The questionnaire is completed by the nursing staff and varies from the highest QoL (score 120) to the lowest QoL (score 0).

### Assessment of ADL

#### Katz index

The Katz index is a 6-item measure of basic human activities of daily living: bathing, dressing, toileting, transfer, continence and feeding [112]. The scale is completed by the nursing staff and varies from complete independency (score 6) to maximum dependency (score 18).

### Assessment of pain

Pain will be assessed by the following pain scales:

#### Coloured analogue scale (CAS)

The CAS will be used to determine both pain intensity and unpleasantness, i.e. affect [113]. The CAS includes 2 pain thermometers which are white at the bottom and red at the top to measure both aspects of pain. It was originally developed to measure pain in young children, but it has also been used in elderly with dementia [114]. The psychometric properties of CAS are comparable to those of visual analogue scales [113]. Participants are instructed to rate both the pain intensity and the unpleasantness of the pain from which they suffer at that moment. On the back of the thermometers a value is given to the pain aspects from 0 (no pain/no affect) to 10 (highest pain intensity/highest affect).

#### Faces pain scale (FPS)

The FPS is an instrument to assess the severity of pain on a scale with 7 faces, ranked in order of pain [115]. The participant's score corresponds to the scale number, ranging from 0 (neutral face) to 6 (extreme painful face). It was originally developed to measure pain in young children, but the FPS has also been used in elderly people with dementia [114].

### Statistical analysis

Comparability between the intervention group and the control group will be assessed at baseline to check for differences between the groups on characteristics that may influence the results on the outcome variables. Scores on neuropsychological tests will be converted into z scores and, according to factor analysis, summed up to form specific cognitive domains. A two-way repeated measurement design (T1-T6), with time as within group factor and group (intervention vs control) as between group variable, will be used to analyse the effect of the intervention on the outcome variables.

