**Discussion:**

This study evaluates the effect of regular walking as a treatment for older people with dementia. The strength of this study is that 1) it has a longitudinal design with multiple repeated measurements, 2) we assess many different health aspects, 3) the intervention is not performed by research staff, but by nursing staff which enables it to become a routine in usual care. Possible limitations of the study are that 1) only active minded institutions are willing to participate creating a selection bias, 2) the drop-out rate will be high in this population, 3) not all participants will be able to perform/understand all tests.

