## Methods/design

### Participants

Participants are older mobile people with dementia who are visiting day care or living in a home for the elderly or nursing home in the Netherlands. Inclusion criteria are 1) a diagnosis of dementia or presence of cognitive impairment that is reported in the medical status and 2) ambulatory with or without walking aid (walker or cane). Exclusion criteria are the presence of personality disorders, cerebral traumata, hydrocephalus, neoplasm, disturbances of consciousness and focal brain disorders.

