#### Key search

The key search test is also a subtest of the BADS [82] and is used to measure how well the participant is able to prepare an efficient plan of action in the context of a routine event [83]. The patient is asked to imagine that a 100-mm square on an A4 size paper is a large field, in which they have lost their keys. They are asked to draw a line, beginning at a black dot, 50 mm below the square, to show the strategy they would use to search the field, to make absolutely certain that they would find their keys. The test evaluates a person's ability to monitor and evaluate their own performance, taking into account factors that are not explicitly stated in the instructions. Their search strategy score is based on a number of criteria, such as efficiency and effectiveness. The best strategy score is 15 and the worst score is 2.

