#### Digit span (forward and backward)

The digit span is a subtest from the Wechsler Memory Scale-Revised (WMS-R) [84]. In the digit span forward, increasingly long sequences of random numbers are orally presented at a rate of one digit per second to the participants, who have to repeat the sequence immediately after oral representation. In the digit span backward, participants have to repeat the sequence in reverse order. To do this, participants perform extra mental operations on the information that is being held in short term memory. While the backward condition is often hypothesized as tapping more into EF than the forward condition which should measure more short term memory, research has failed to demonstrate this result [85,86]. These studies suggest that both conditions tap into EF. Each condition ends when a participant fails to recall at least two strings of the same length or repeated an eight-digit sequence correctly. The minimal score for both conditions is 0 and the best score is 21.

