#### Stroop task

The version of the Stroop task that is commonly used in the Netherlands [94] consists of three subtasks which the participant performs as quickly as possible; each test has a 45 second time limit. In the first subtask, participants are presented with four color words, i.e. red, green, blue and yellow, printed in black ink in ten rows with ten names each. The participant's task is to read as many color names in the right order. Second, the participant is presented with a similar paper, but this time with solid color patches (red, green, blue and yellow) that have to be named in the right order. In the final subtask the names of the colors are written in a different color ink than the meaning of the word (i.e. the word 'blue' written in red ink) and the participants again need to name the color of the ink, thus suppressing reading the word, which is a highly automatic reaction. This test has been found to correlate moderately well with other tests of response inhibition [95], which is an EF task [96]. The score on each card is the total correct mentioned colors within 45 seconds. The final score is the score on card 2 minus the score on card 3. A lower final score indicates a better performance of inhibition.

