## Discussion

This paper presents the design of a RCT, which aims to explore the longitudinal effect of regular walking on several health aspects of older people with dementia. The strength of this study is that 1) the intervention is not performed by the research staff, but by the nursing staff which enables it to become a routine in usual care, 2) we have a high number of repeated measurements, i.e. one baseline and 6 post measurements, 3) the various outcome variables enables us to analyse the development of different health aspects within 18 months.

Possible limitations of this study are that 1) only active minded institutions are willing to participate creating a selection bias, 2) there will be a (high) drop-out rate, for example due to death, 3) not all participants will be able to perform/understand all tests.

This method is appropriate to collect data on the effectiveness and feasibility of a walking program. It is also interesting to examine what aspects determine the compliance of the participants. Due to the aging and dementia process, it is not always necessary to increase in test score to find an effect of the intervention, but stabilizing cognitive and behavioural functioning in those who participate in the walking group would also be worthwhile.

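### Cognitive domain scores are defined as a sum of z scores, which is not comparable between participants who complete different numbers of tests

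*Protocol article*

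**What the plan says.** The Statistical analysis section fixes how the neuropsychological tests are combined: "Scores on neuropsychological tests will be converted into z scores and, according to factor analysis, summed up to form specific cognitive domains". The operation is a sum. The article does not say what happens to a domain when one of its tests was not done, or whether scores are put in the same direction first.

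The abstract and the main Discussion both list as a limitation that "not all participants will be able to perform/understand all tests". Neither gives a share. Entry requires "a diagnosis of dementia or presence of cognitive impairment that is reported in the medical status", with no upper limit on severity, and the staging scale under Stage of dementia runs to the profound stage. Testing is repeated at seven visits over 18 months.

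Under Stroop task the outcome is a difference: "The final score is the score on card 2 minus the score on card 3". The article adds: "A lower final score indicates a better performance of inhibition". Other cognitive tests with a stated range run the opposite way. For Key search, "The best strategy score is 15 and the worst score is 2"; for Digit span, "The minimal score for both conditions is 0 and the best score is 21".

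**The concern.** A z-score sum has a common meaning only if everyone contributes the same number of tests. The authors themselves expect incomplete batteries. In a progressive disease the gaps will plausibly fall mostly on the most impaired and become more frequent over follow-up.

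A sum then leaves two options. Adding up whatever was done gives each missing test z = 0, the sample average, so a person who could not do a test scores better than one who did it badly. Requiring the full set removes such people from the domain. Cognition is the outcome from which the sample size was derived, so either loss falls on the comparison the trial was sized for.

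**Working it through.** **The plan's own figure.** The sample size does not depend on this point, but it reproduces. Inputs from Sample size: f = 0.32, alpha 0.05, power 0.80, 7 measurements, 2 groups. The multivariate form of the group-by-time test has noncentrality N × f², df1 = 6 and df2 = N − 2 − 6 + 1. It first reaches 0.80 at N = 140 (noncentrality 140 × 0.1024 = 14.3, df2 = 133), which is 70 per group as stated.

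**Summing the available tests.** A participant averaging z on the m tests done out of k scores m × z instead of k × z, so the fraction m/k of the deficit remains. At z = −1.5 on every test of a 4-test domain:
- all four done: sum −6, mean −1.5;
- two done: sum −3, mean −1.5.

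A simulation shows the same. Its assumptions, none from the article, are 4 tests, inter-test correlation 0.6, and the least able 5% to 30% lacking two tests.

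| Share lacking 2 of 4 tests | Their true sum | Sum of available tests | 4 × mean of available tests |
|---|---|---|---|
| 5% | −6.40 | −3.20 | −6.41 |
| 10% | −5.43 | −2.72 | −5.43 |
| 20% | −4.33 | −2.17 | −4.33 |
| 30% | −3.59 | −1.79 | −3.59 |

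The mean is not a perfect repair. The two missing tests are standardised on those who could do them, which lowers the other participants' average from 0.33 to 0.17 (5% row) and from 1.53 to 0.77 (30% row). The gap between the two sets of participants is then:
- 5% row: true 0.33 + 6.40 = 6.73; sum 0.17 + 3.20 = 3.37 (50%); mean 0.17 + 6.41 = 6.58 (98%).
- 30% row: true 1.53 + 3.59 = 5.12; sum 0.77 + 1.79 = 2.56 (50%); mean 0.77 + 3.59 = 4.36 (85%).

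**Dilution of a benefit.** If walking helps equally on every test and a share p of participants has half the tests, the average raw benefit on the sum is (1 − p) + p/2 = 1 − p/2 of its full value: 0.975 at p = 5% and 0.85 at p = 30%. The SD of the sum changes too, so these are not power figures.

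**Requiring every test.** With a fraction q missing per test, independently, the share of 4-test scores lost is 1 − (1 − q)^4. The last column applies this to the 140 participants the sample size requires.

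| q (assumed) | Scores lost | Scored out of 140 |
|---|---|---|
| 5% | 1 − 0.95^4 = 19% | 114 |
| 10% | 1 − 0.90^4 = 34% | 92 |
| 20% | 1 − 0.80^4 = 59% | 57 |

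If the same people miss every test, the loss falls to q itself.

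**Direction.** Assume k tests, common correlation r once aligned, and an equal benefit d on each. The standardised effect of the aligned sum is k·d / √(k + k(k − 1)r). With one test left unreversed it is (k − 2)·d / √(k + (k − 1)(k − 4)r). At r = 0.5 and d = 0.5:
- 2 tests: 0.577 falls to 0;
- 3 tests: 0.612 falls to 0.354, ratio 0.58;
- 4 tests: 0.632 falls to 0.500, ratio 0.79;
- 5 tests: 0.645 falls to 0.567, ratio 0.88.

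For r from 0.3 to 0.6 the ratios run 0.47–0.64, 0.69–0.84 and 0.80–0.91 for 3, 4 and 5 tests.

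**The case against.** The article compresses the analysis into a few sentences. Handling of missing tests, sign alignment and the reference for the z scores commonly sit in a full protocol or analysis plan that is not shown, and their absence here is no fault. That is right. The word summed, however, is not an absence. It is a stated choice, and a poor one for the incomplete batteries the authors predict.

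Inability need not mean a missing score. Digit span has a floor ("The minimal score for both conditions is 0 and the best score is 21"), and several other tests are counts, so an attempted but failed test can enter as a low z score. This stands and would reduce the problem. It does not help with a test that is not administered or not understood, and the article does not say which tests would be scored at their floor.

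Several stronger readings are tempting, but the documents do not support them:
- **Many participants will be unable to do the tests.** The article says only that not all will be able, and gives no share.
- **The Stroop will be summed unreversed.** Nothing says so. Reversal is routine, the authors state the direction themselves, and a factor analysis would show the opposite-sign loading. An error would reach only the domain containing the Stroop, and would affect all participants there, not mainly the most impaired. Nor is every other test documented as better when higher: Rule shift cards has no stated scale direction.
- **Change over time is removed by standardising at each visit.** The article does not say the z scores are formed that way. Even if they were, standardising both arms together would keep the difference between arms at each visit.
- **The sum creates a spurious treatment effect.** That needs test completion to differ between arms, and the article offers no evidence that it will.

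**Conclusion.** The point holds as a criticism of the stated composite. Under a sum, the deficit of participants lacking tests shrinks in proportion to the tests missing, by half when half are missing; if complete sets are required, these participants drop out. The 34% loss rests on 4 tests, 10% missing per test and independence. It ranges from 19% to 59% for 5% to 20% missing, and is smaller if gaps cluster in the same people.

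Under randomisation the expected harm is dilution and lost precision for cognition. Its effect on power cannot be sized from the article, because neither the number of tests per domain nor the share missing is given. The direction of the Stroop is a matter to confirm, not a demonstrated error.

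**What to change.** In the Statistical analysis section, replace the sum by the mean of the available z scores in each domain and state:

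1. Every visit is standardised to the pooled T0 mean and SD of both arms.
2. A domain score needs a minimum share of its tests, for example half.
3. All scores are aligned in direction before averaging, with the Stroop difference reversed. Reversal alone does not cure the Stroop's floor: someone scoring 0 on both cards gets a difference of 0, against 30 for someone scoring 60 and 30, and so would appear to have the better inhibition. A rule for very low card scores should go with it.

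A sensitivity analysis that gives the lowest score to a test not done because of cognitive impairment would cover what the mean cannot recover.

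The cost is wording only, with no new data or visits. A mean over fewer tests is slightly noisier, and the minimum-share rule will still leave some participants without a domain score.

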### Sample size

Sample size calculation was performed using the statistical power analysis program G*Power 3.1 [52] which has the possibility to perform power analyses for a repeated measures design with a between group variable. Based on two meta-analyses studying the effect of physical activity on cognition [16,24], the estimated effect size in this study is expected to be moderate to large (Cohens f = 0.32). Using a type 1 error of 0.05, a power of 0.80, seven repeated measurements and 2 groups, a sample size of 70 in each group is required. Taking into account an attrition rate of 25%, 175 participants should be included in this study.

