### Procedure

The outcome variables are measured at baseline (pre-treatment: T0), after 6 weeks of intervention (post-treatment: T1) and after 3 (T2), 6 (T3), 9 (T4), 12 (T5) and 18 (T6) months of intervention. Trained experimenters, blinded to the intervention assignment, will administer the neuropsychological tests, physical tests and level of depression, anxiety and pain. The nursing staff fills in questionnaires to measure QoL, ADL and define the stage of dementia. The other variables are objective measurements.

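### The T1-T6 repeated-measures model does not say whether the group term or the group-by-time term is the intervention effect, and the term that reproduces the sample size cannot show a benefit that is present by T1 and then sustained

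*Protocol article*

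**What the plan says.** The Procedure section schedules a baseline (T0) and six later assessments: "after 6 weeks of intervention (post-treatment: T1) and after 3 (T2), 6 (T3), 9 (T4), 12 (T5) and 18 (T6) months of intervention". The Statistical analysis section then takes T1 to T6 as the levels of the time factor in a two-way repeated-measures design, "with time as within group factor and group (intervention vs control) as between group variable, will be used to analyse the effect of the intervention". It does not single out the group term, the group-by-time term or a visit.

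The Sample size section names the software, which "has the possibility to perform power analyses for a repeated measures design with a between group variable", and takes Cohen's f as 0.32. Its other inputs and its result are: "Using a type 1 error of 0.05, a power of 0.80, seven repeated measurements and 2 groups", giving 70 per group. It does not say which effect f describes or which test the power belongs to. Neither the aim at the end of the Background nor the Discussion names a deciding term or visit; both speak of a longitudinal effect.

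**The concern.** A model with group and time as factors gives two between-group tests, and they answer different questions. The group term asks whether the arms differ on average over the visits in the model. The group-by-time term asks whether the difference changes between those visits. It says nothing about direction, and it is blind to a difference that stays constant.

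Whether T0 is a level of the time factor therefore matters a great deal. With T0 included, a benefit that appears by T1 and persists is a change over time and shows in the interaction. With T0 left out, as the section states, the same benefit is a constant gap and shows only in the group term.

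Two things are at stake. The trial could be analysed with the test it appears to be sized on and miss a lasting benefit. Or, with the deciding term left open, whichever term is significant could be reported as the planned result.

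**Working it through.** **Inputs from the Protocol article.** f = 0.32 (f² = 0.1024), alpha 0.05, power 0.80, m = 7 measurements, 2 groups, 70 per group (N = 140); analysis over T1-T6 (m = 6).

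**Assumptions.** Equal variances, equal correlation ρ between visits, no drop-out. The document gives no ρ; 0.5 is used, with a range.

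**1. Which test gives 70 per group?**
- Multivariate group-by-time test, m = 7: df = 6 and N − 7, noncentrality λ = f²N. At N = 140, λ = 0.1024 × 140 = 14.34, df 6 and 133, power 0.802. At N = 139 power is 0.798. So 140 is reproduced exactly.
- Univariate group-by-time test with the same λ: N = 136, close to 140.
- Group term, m = 7: λ = f²·N·m / (1 + (m − 1)ρ). At ρ = 0.5 and N = 46, λ = 0.1024 × 46 × 7 / 4 = 8.24, df 1 and 44, power 0.802. So 46 in total suffices. Even at ρ = 0.99 the figure is 78. The group term does not lead to 140.

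The stated size therefore corresponds to a group-by-time test over T0-T6.

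**2. What does each term detect over T1-T6?** With n = 70 per arm and true visit differences δ₁…δ₆ in SD units:
- Group term: noncentrality = mean(δ) × √(n/2) / √((1 + 5ρ)/6). At ρ = 0.5 the denominator is √(3.5/6) = 0.764, and √35 = 5.916.
- Group-by-time term: λ = (n/2) × Σ(δⱼ − mean δ)² / (1 − ρ), df 5 and 134.

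| True pattern, ρ = 0.5 | Group term | Group-by-time term |
|---|---|---|
| 0.4 SD at all of T1-T6 | 0.4 × 5.916 / 0.764 = 3.10; power 87% | Σ = 0, λ = 0; power 5% |
| 0.5, 0.4, 0.2 SD at T1-T3, then none | 0.183 × 5.916 / 0.764 = 1.42; power 29% | 35 × 0.2483 / 0.5 = 17.4; power 90% |

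For the sustained pattern the 5% does not depend on ρ, because λ is zero whatever ρ is. The group-term power runs from 95% at ρ = 0.3 to 69% at ρ = 0.9 by the same formula.

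**3. Error rate if either term may count.** Two independent tests give 1 − 0.95² = 0.0975. Simulated null trials (70 per arm, six visits, 20,000 per setting, equal or autoregressive correlation of 0.3 to 0.9) gave 0.094 to 0.100 for at least one of the two significant. Taken alone, the group test gave 0.048 to 0.052 and the interaction test 0.047 to 0.052.

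**4. One late visit as the contrast.** For 0.4 SD at T6 alone, unadjusted: 0.4 × 5.916 = 2.37, power about 65%.

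**The case against.** The strongest reply is that this is a condensed article. The deciding term is often fixed in the full protocol or analysis plan, and a group and time model does address the intervention effect. The sample size arithmetic and the longitudinal framing also both point to the interaction, so one could say the intended test is clear.

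The first part stands as far as it goes: silence on a contrast would not by itself be a finding. But the stated parts do not fit together. The arithmetic points to an interaction over seven measurements, and the analysis section states six. The interaction means something different once T0 is out, so the intended test cannot be inferred by combining the two sections.

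Some stronger readings are tempting but unsupported:
- That the 5% level is lost outright. Each term alone keeps it; the inflation arises only if more than one term may be claimed as the result, and no section states such a rule.
- That six visit-by-visit comparisons add to the error. The document does not plan them.
- That a stable course in the walking group alone would count as success. The Discussion does say that "stabilizing cognitive and behavioural functioning in those who participate in the walking group would also be worthwhile", but this is a remark that scores need not rise in a declining population. It is not a decision rule, and the analysis section fixes group as a between-group factor.
- That calling T1 post-treatment makes six weeks the deciding visit. It is a label that no analysis uses, and the same sentence counts later visits as months of intervention.

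**Conclusion.** The point holds in this form: the document states one alpha, one power and one model without saying which of the model's two between-group terms they belong to, and its own figures pull in different directions. The interaction reproduces the sample size, but under the stated T1-T6 analysis it has no power beyond the 5% false-positive rate for a benefit that is constant from T1. That result needs no assumption about correlation. The 87% for the group term rests on 0.4 SD, 70 per arm, no drop-out and a correlation of 0.5. The error rate of about 0.10 is conditional on either term being allowed to count, and it concerns one outcome; multiplicity across outcomes is a separate matter. That an interaction over T0-T6 was intended is an inference from the arithmetic, not something the text says.

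**What to change.** In the Statistical analysis section, name one 1-degree-of-freedom between-group contrast per outcome, adjusted for the T0 score and tested two-sided at 0.05. Examples are the average walking-minus-control difference over T1-T6, or the difference at one named visit. Label the remaining terms, including the group-by-time test, as supportive. In the Sample size section, state which test the 0.80 power refers to and restate the calculation for the named contrast.

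This is a change of wording, with no new visits, data or participants implied at the assumed f: the group main effect needs at most about 80 in total. The cost depends on the contrast. With the average difference, a benefit confined to the early visits would be supportive only. A T6-only contrast speaks directly to 18 months but is weaker, at about 65% unadjusted for 0.4 SD against about 87% for the average. Drop-out, which the authors expect to be high, would lower it further.

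### The two-way repeated-measures analysis, in its usual form, drops participants with any missing visit; a likelihood-based mixed model would keep them in a trial that expects high drop-out

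*Protocol article*

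**What the plan says.** The Statistical analysis section gives one method for the outcome variables, a two-way repeated-measures layout that carries the label T1-T6 and is described as follows: "with time as within group factor and group (intervention vs control) as between group variable, will be used to analyse the effect". It does not use the word ANOVA, does not restrict the analysis to complete cases, and does not say what happens to a participant with a missing visit.

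The Sample size section uses G*Power for "power analyses for a repeated measures design with a between group variable". The inputs are Cohen's f of 0.32, "Using a type 1 error of 0.05, a power of 0.80", and "seven repeated measurements and 2 groups, a sample size of 70 in each group is required". For 25% attrition the total is raised to 175.

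The Procedure section sets seven assessments, from baseline (T0) to 18 months (T6). The abstract's discussion warns that "the drop-out rate will be high in this population". The main Discussion repeats that "there will be a (high) drop-out rate, for example due to death", and adds that some participants will be unable to perform or understand every test.

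**The concern.** Time as a within factor and group as a between factor is the vocabulary of classical repeated-measures (M)ANOVA. Standard implementations need a full set of visits for each participant. One missed visit, or one session at which the person could not be tested, removes that person from the analysis of that outcome, together with everything recorded earlier.

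That fits poorly with 18 months of follow-up in people with dementia, where the article predicts heavy loss, some of it through death. Two things are at stake. The first is information: visits already collected are thrown away. The second is the comparison itself. Completers are a subset selected after randomisation, and the arms differ in burden (supervised walks five times a week against sedentary gatherings three times a week), so the reasons for leaving could differ between them.

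**Working it through.** **Step 1: reproduce the plan's figure.** Inputs from the Sample size section: f = 0.32, alpha 0.05, power 0.80, 2 groups, m = 7.
- Multivariate group-by-time test: noncentrality = f² × N, with m − 1 = 6 and N − 7 degrees of freedom.
- At N = 140: 0.1024 × 140 = 14.34, df 6 and 133, power 0.802. At N = 139 power is 0.798. The minimum is therefore 140, or 70 per group, as stated.
- The univariate version with the same noncentrality and sphericity gives 136.
- Other readings of f are far off. At a within-person correlation of 0.5, the between-group test needs 46 in total and the G*Power default interaction about 12.

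The stated sample size therefore matches a classical test that needs complete vectors of visits.

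**Step 2: completers at the plan's own attrition.** 175 × 0.75 = 131.25, so about 131 complete and 44 excluded. At N = 131 power is 0.768 (multivariate) or 0.789 (univariate). Part of this shortfall comes from how attrition was added: 140 × 1.25 = 175, whereas 140 / 0.75 = 187. That is a separate point.

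**Step 3: add intermittent missingness.** The article gives no rate, so p = 2% to 10% at each of the six follow-ups is assumed, independent of drop-out. Complete cases = 175 × 0.75 × (1 − p)^6. Power is for the multivariate test.

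| p per visit | Fraction complete | Complete cases | Power |
|---|---|---|---|
| 0% | 0.75 | 131 | 0.77 |
| 2% | 0.66 | 116 | 0.70 |
| 5% | 0.55 | 96 | 0.60 |
| 10% | 0.40 | 70 | 0.44 |

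**Step 4: bias among completers, by simulation.** Every parameter here is assumed.
- *Set-up A.* Unit-SD scores, constant correlation 0.7, a decline of 1 SD over 18 months, no true effect, about 25% drop-out per arm. Drop-out follows a logistic model in the last observed score in the walking arm only. Completers show about 0.16-0.18 SD in favour of walking at T6. With this correlation structure the difference in change from baseline is about zero. A weaker dependence on score gives less.
- *Set-up A with the same rule in both arms.* The T6 bias is near zero.
- *Set-up B.* Random intercepts and slopes, true T6 difference 0.30 outcome units, drop-out depending more strongly on score in the control arm (41% against 31% incomplete). The completers' T6 difference is 0.08, so the error now goes against walking. The difference in change from baseline is 0.27.
- *Likelihood-type estimation on all observed visits* recovers the true difference in both set-ups (0.00 in A, 0.30 in B). This is expected, because drop-out was made to depend only on observed scores, so missing at random holds by construction.

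A sample size for the mixed model cannot be computed, because the article gives neither a within-person correlation nor a drop-out pattern.

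**The case against.** A reader might infer that the plan commits to a complete-case analysis. It does not say so. Group, time and their interaction also describe a mixed model, and this is a condensed article whose full analysis plan is not shown. That stands, and it limits confidence to moderate. It does not remove the point: the one method named is the classical form, the sample size reproduces with the test that needs complete data, and the fit between that method and the predicted losses can be judged from the article alone.

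Inflating for attrition is routine under any analysis, so the step from 140 to 175 does not show that incomplete cases will be deleted. That also stands. The supporting evidence is the match of 140 to the multivariate test, and that shows which power model was used rather than how missing data will be treated.

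A further tempting reading is that the randomised comparison becomes a biased, survivors-only one that flatters walking. The documents do not support this. Nothing in them says that drop-out will differ by arm, bias is near zero if it does not, and a different arm-specific mechanism reverses the sign. Survivors-only is also the wrong term, since living participants with one missed visit would be excluded too.

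Finally, a likelihood model does not settle death: it implicitly carries trajectories past it. This is correct, and the analysis text should say so.

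**Conclusion.** The point holds as a mismatch between the named method and the data the article predicts. It should be fixed, as a cheap improvement, with moderate confidence.

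- *Loss of data:* certain if the analysis is run in its usual form. At most about 131 of 175 contribute at 25% attrition, with power about 0.77. The count falls to between 116 and 70 under the assumed 2-10% intermittent missingness.
- *Bias:* conditional. It requires drop-out that depends on scores differently in the two arms. Under assumed parameters it is then about 0.15-0.2 SD in the T6 difference in level, small in change from baseline, and of unknown direction.

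Because the distortion lies mainly in level, the T1-T6 label matters. It leaves out T0, while the sample size counts seven measurements; the two passages need reconciling.

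**What to change.** In Statistical analysis, replace the two-way repeated-measures method with a likelihood-based linear mixed model for repeated measures, with group, categorical visit and their interaction. Include all participants as randomised and all available visits from T0 to T6, with baseline in the model. This also removes the mismatch between T1-T6 and seven measurements.

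Alongside it:
- report deaths and other losses by arm;
- state that the model estimate does not by itself resolve outcomes truncated by death;
- add one sensitivity analysis in which drop-outs follow worse trajectories than those who remain.

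The cost is a change of wording and slightly more programming, with no new data. The downside is reliance on missing at random, which is a weaker assumption than the complete-case analysis needs. The form of the covariance matrix is secondary and can be left to the analysis plan.
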